#### 9.1.2 Erlotinib and Vinorelbine pharmacokinetics

##### Vinorelbine

Blood samples (3mL) will be obtained on day 1 and day 10 of dosing at the following time points:

Day 1: 0 hr (pre-dose), 30min, 1hr, 2hr, 4hr, 6hr, 8hr, 24hr, 48hr

Day 10: 0 hr (prior to dosing), 30min, 1hr, 2hr, 4hr, 6hr, 8hr, 24hr

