### 1.2 Secondary Objectives

- To assess for pharmacokinetic interaction of erlotinib on navelbine
- To assess the usefulness of circulating endothelial cells (CECs) and circulating endothelial progenitor cells (CEPs) as surrogate biomarkers to determine optimal anti-angiogenic effect of treatment
- To evaluate the clinical benefit rate (CR+PR+SD) and overall survival

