### **Pharmacokinetics**

Following oral administration, NAVELBINE® is promptly absorbed and the Tmax is reached within 1.5 to 3 hours with a blood concentration peak (Cmax) of approximately 130 ng/mL after dosing at 80 mg/m^2. The absolute bioavailability is about 40% and simultaneous intake of a low fat standard meal does not modify the area-under the concentration-time curve (AUC). The effect of a high fat meal on absorption has not been studied.

NAVELBINE® Oral 60 and 80 mg/m^2 leads to a comparable AUC to that obtained from 25 and 30 mg/m^2 of the IV formulation respectively. Interindividual variability of the AUC is similar after administration by both the IV and oral routes. There is a proportional increase between the AUC and dose. The mean pharmacokinetic parameters were evaluated in blood. After intravenous administration, the terminal half-life averaged 38 hours. Blood clearance was high, approached liver blood flow and averaged 0.72 L/hr/kg (range: 0.32 - 1.26 L/hr/kg), while steady state volume of distribution was large, averaged 21.2 L/kg (range: 7.5 - 39.7 L/kg), and indicated extensive tissue distribution.

Vinorelbine binds extensively to blood cells and especially platelets (70-80%), but less extensively (about 15%) to plasma proteins. There is a significant uptake of NAVELBINE® in lungs, as assessed by pulmonary surgical biopsies showing up to a 300 fold greater concentration than in serum. NAVELBINE® has not been detected in the central nervous system.

NAVELBINE® is mostly metabolised by the CYP 3A4 isoform of the cytochrome P450. All the metabolites have been identified, and none are active except 4-O-deacetylvinorelbine, which is the main metabolite in blood. No sulfo or glucurono conjugates are observed. Renal elimination is low (<20% of the dose) and consists mostly of the parent compound. Biliary excretion is the predominant elimination route of both metabolites and unchanged NAVELBINE®, which is the main recovered compound. The effect of renal dysfunction on NAVELBINE® disposition has not been assessed, however dose reduction in the presence of renal insufficiency is not indicated with

NAVELBINE® due to its low renal elimination.

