Reported adverse events and potential risks for Oral Vinorelbine and Erlotinib are described in Section 5.2. Appropriate dose modifications for Oral Vinorelbine and Erlotinib are described in Section 6. No investigational or commercial agents or therapies other than those described below may be administered with the intent to treat the patient's malignancy.

| REGIMEN DESCRIPTION |                                                                                                                                                                                                  |                                             |              |                                                                                                                                      |                     |
|----------------------------|--------------------------------------------------------------------------------------------------------------------------------------------------------------------------------------------------|---------------------------------------------|--------------|--------------------------------------------------------------------------------------------------------------------------------------|---------------------|
| Agent               | Premedications; Precautions                                                                                                                                                               | Dose                                 | Route | Schedule                                                                                                                      | Cycle Length |
| Vinorelbine                | Both erlotinib and vinorelbine will be given after prophylactic administration of antiemetics (preferably 5-HT 3 antagonist) on Day 1 (except for Cycle 1) and on Day 8 of each cycle | Dose as appropriate for assigned dose level | Oral         | Conventional Schedule: Day 1 and 8 of each cycle
Metronomic Schedule: D1,3,5 every 7 days for 3 weeks of each cycle | 21 days (3 wks)     |

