## **13.1 Analysis**

- The primary aim of this study is to determine the dose limiting toxicities of oral vinorelbine combined with erlotinib and the maximal tolerated dose (MTD) of this drug combination in patients with non-small cell lung cancer. The toxicity profile will be graded as described above and reported with the corresponding dose level.
- The MTD will be dose at which less than 2 DLTs occur. Steady state plasma drug

concentrations, area under the curve values, volume of distribution and clearance of oral vinorelbine and erlotinib in each patient will be calculated and correlated with dose. These quantities will be summarized for all patients.

- Response rates (Complete response, partial response, stable disease) to study treatment will be described based on RECIST criteria and summarized by dose. Overall survival will be measured from registration to death and analyzed by the Kaplan-Meier method.
- Exploratory analysis of known functional SNPs in the transporter genes will be described in relation to dose and response. An exploratory analysis of the changes on CEC/CEP assessment of angiogenesis in each group would be performed.

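### The day-10 vinorelbine profile does not fall on a dosing day in the conventional schedule, so that schedule yields no paired profile with erlotinib

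*Protocol*

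**What the plan says.** The first secondary objective in section 1.2 is "To assess for pharmacokinetic interaction of erlotinib on navelbine". It names no schedule.

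The regimen table in section 5.1 gives conventional-schedule vinorelbine on "Day 1 and 8 of each cycle" and metronomic vinorelbine on "D1,3,5 every 7 days for 3 weeks of each cycle". The dose table in section 6 agrees. Erlotinib starts on day 3, and section 9.1.2 says that this is so that vinorelbine can first be profiled alone.

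Section 9.1.2 then gives one vinorelbine timetable without distinguishing the schedules: "Blood samples (3mL) will be obtained on day 1 and day 10 of dosing at the following time points". The two profiles are "Day 1: 0 hr (pre-dose), 30min, 1hr, 2hr, 4hr, 6hr, 8hr, 24hr, 48hr" and "Day 10: 0 hr (prior to dosing), 30min, 1hr, 2hr, 4hr, 6hr, 8hr, 24hr". Day 10 is also the day chosen for the steady-state erlotinib profile.

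Section 13.1 says that AUC, volume of distribution and clearance of both drugs "in each patient will be calculated and correlated with dose".

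**The concern.** The design is a within-patient comparison: vinorelbine alone on day 1, then vinorelbine with erlotinib near steady state. Day 10 suits erlotinib. It is not a vinorelbine dosing day in the conventional schedule, so the pre-dose label and the samples at 30 min to 8 h refer to a dose that is not given. Oral Tmax is 1.5 to 3 h (section 2.1.1), so those dense early times would record only a declining tail.

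This is lost at the time of sampling. No analysis can later recover an absorption phase that was not sampled. The question has substance, because section 2 describes both drugs as cleared mainly through CYP3A4 and reports a strong relation between vinorelbine AUC and falls in leucocytes or neutrophils.

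The metronomic schedule has a milder problem. Day 10 is a real dosing day, but drug remaining from earlier doses raises the day-10 exposure even if erlotinib has no effect.

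**Working it through.** **Inputs, all from the protocol.** Vinorelbine: "After intravenous administration, the terminal half-life averaged 38 hours"; clearance 0.72 L/h/kg; steady-state volume 21.2 L/kg; AUC proportional to dose (section 2.1.1). Erlotinib: median half-life 36.2 h, steady state in 7 to 8 days (section 2.1.2), first dose on day 3.

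**The plan's own figure.** 5 × 36.2 h = 181 h = 7.5 days, which reproduces the 7 to 8 days. The fraction of steady state before the day-10 dose is 1 − 2^(−168/36.2) = 0.96. Day 10 is therefore reasonable for erlotinib.

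**Dosing days.**
- Conventional: days 1, 8, 22, 29. Day 10 is not among them.
- Metronomic: days 1, 3, 5, 8, 10, 12, 15, 17, 19. Day 10 is among them.
- If day 10 of dosing meant the tenth erlotinib day (study day 12), the conventional schedule would still have no dose.

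**Conventional schedule.** Day 10 at 0 h is 48 h after the day-8 dose, and the last sample is at 72 h. The only post-dose time shared with day 1 is 48 h. At that point the terminal-phase level from the day-8 dose is 2^(−48/38) = 0.417, and the day-1 dose adds 2^(−216/38) = 0.019, about 2% of one dose. The 48–72 h window holds about 7 to 8% of AUC to infinity under the biexponential model below (first-phase half-life 1 to 4 h).

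**Metronomic schedule, no interaction, equal doses.** Terminal-phase residue on day 10 from the doses on days 1, 3, 5 and 8 (216, 168, 120 and 48 h earlier):

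0.019 + 0.047 + 0.112 + 0.417 = 0.595 of one dose.

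The effect on the day-10/day-1 AUC0-24 ratio depends on the model:

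| Model | Ratio |
|---|---|
| Biexponential, matching half-life, clearance and volume | 1.14 to 1.17 |
| One compartment, half-life ln2 × 21.2/0.72 = 20.4 h | 1.22 |
| One compartment, half-life 38 h | 1.59 |

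The biexponential row fixes the terminal half-life at 38 h and the mean residence time at 21.2/0.72 = 29.4 h. The first-phase half-life is not in the protocol; it is assumed to lie between 0.5 and 8 h. Example at 4 h: mean residence times of the two phases are 4/ln2 = 5.77 h and 38/ln2 = 54.8 h, so the terminal share of AUC to infinity is (29.4 − 5.77)/(54.8 − 5.77) = 0.483. Single-dose AUC0-24 is 0.517 × (1 − 2^(−24/4)) + 0.483 × (1 − 2^(−24/38)) = 0.509 + 0.171 = 0.680. Carry-over is 0.595 × 0.171 = 0.102. The ratio is 1 + 0.102/0.680 = 1.15.

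**Alternative days for the conventional schedule.**

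| Day | Erlotinib, fraction of steady state | Vinorelbine residue, terminal phase |
|---|---|---|
| Day 8 | 1 − 2^(−120/36.2) = 0.90 | 2^(−168/38) = 0.047 |
| Cycle 2 day 1 (day 22) | 1 − 2^(−456/36.2) = 0.9998 | 2^(−336/38) + 2^(−504/38) = 0.002 |

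**The case against.** A reader might infer that the interaction objective cannot be answered at all. The documents do not support that. The objective names no schedule. The metronomic schedule has a real day-10 dose, a pre-dose sample, a 24 h profile, a day-1 profile without erlotinib, and stated dose proportionality. Carry-over there is a bias that can be corrected. Nor is the conventional schedule wholly empty: the matched 48 h point and the 48–72 h slope carry limited clearance information.

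A reader might also take 59% as the size of the carry-over bias. That figure requires one compartment at 38 h, which does not fit the protocol's own clearance and volume. Models that respect those two figures give 14 to 22%.

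Section 13.1 might be read as ruling out an interaction analysis, because it mentions only correlation with dose. It does not exclude a day-1/day-10 comparison. The estimator, the carry-over correction and dose normalisation may properly sit in an analysis plan that is not at hand, so their absence is not counted as an error.

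The metronomic doses might be said to differ between day 1 and day 10. Weekly totals of 80, 100, 140 and 160 mg cannot be divided into three equal doses with 20 and 30 mg capsules. The protocol does not state the split, however, and the two days could still carry the same dose.

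All of this stands. None of it touches the conventional-schedule conflict: no analysis plan can supply samples after a dose that was not given.

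**Conclusion.** Sections 5.1 and 6 conflict with section 9.1.2 for the conventional schedule and must be reconciled. Followed as written, the plan yields no profile with erlotinib that covers absorption, Cmax or AUC0-24 in that schedule, and only one matched time point. This follows from the calendar alone and needs no pharmacokinetic model.

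The objective then depends almost wholly on the metronomic schedule. An uncorrected comparison there would suggest 14 to 22% higher exposure with no interaction present, and 59% at the extreme. Those sizes assume equal doses, linear kinetics, intravenous disposition figures applied to the oral drug, absorption time ignored, and the assumed range for the first-phase half-life.

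Only a secondary objective is affected. The dose-limiting toxicity definition, the escalation rules and the determination of the maximum tolerated dose do not depend on these samples.

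**What to change.** Split the vinorelbine timetable in section 9.1.2 by schedule.

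- **Conventional:** move the second vinorelbine profile to a dosing day already in the protocol, with erlotinib on board. Day 8 already has a blood count and offers about 90% of erlotinib steady state with about 5% vinorelbine carry-over. Cycle 2 day 1 (day 22) coincides with the first-cycle erlotinib trough and offers over 99.9% and about 0.2%. Dosing does not change.
- **Metronomic:** keep day 10, record the actual dose taken on days 1 and 10, and correct for the day-10 pre-dose level and the actual dose when comparing with day 1. The method can be set out in the analysis plan.
- **Erlotinib:** the day-10 profile can stay.

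Cost: the number of vinorelbine samples is unchanged, but the visits are not. Seven of the eight day-10 vinorelbine times (all but 30 min) coincide with erlotinib times. If erlotinib stays on day 10, conventional-schedule patients gain a serial-sampling day and a 24 h return. Day 8 accepts erlotinib slightly below steady state; cycle 2 day 1 accepts the loss of patients who stop or are delayed before then.

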##### Erlotinib

Erlotinib will commence on day 3 to allow PK profiling of vinorelbine alone.

Pharmacokinetic analysis for erlotinib and its metabolite, OSI-420 will be done on days 3

(after the first dose) and 10 (at steady state).

Day 3: 0hr (predose), 1hr, 2hr, 4hr, 6hr, 8hr, 24hr.

Day 10: Steady state erlotinib pharmacokinetics will be evaluated on day 10 at the following time points: 0 hr (prior to dosing), 1hr, 2hr, 4hr, 6hr, 8hr, 24hr.

A single steady state trough level of erlotinib will be taken on day 22 of every cycle

### 9.1.3 Pharmacogenetics

Blood samples (6 ml) will be obtained at baseline for pharmacogenetic analysis. Genetic polymorphisms of transporter proteins: ABCG2 and MDR1, along with CYP3A5 will be done to determine any correlation with outcome.

Plasma concentration of vinorelbine and erlotinib is determined centrally at Clinical Pharmacology Laboratory, NCCS by previously optimized methods. SNP analysis of the relevant genes of interest will also be analysed in the Clinical Pharmacology Laboratory, NCCS. The patients will be followed in clinic as per main protocol.

## 10. STUDY CALENDAR

Baseline evaluations are to be conducted within 2 weeks prior to start of protocol therapy. Scans and x-rays must be done  $\leq 4$  weeks prior to the start of therapy. In the event that the patient's condition is deteriorating, laboratory evaluations should be repeated within 48 hours prior to initiation of the next cycle of therapy.

|                    | Pre-Study | Wk 1    | Wk 2 | Wk 3 | Wk 4 | Wk 7 | Wk 10 | Wk 13 | Wk 16 | Wk 19 | Wk 22 | >Wk 25         |  | Off Study d |
|--------------------|-----------|---------|------|------|------|------|-------|-------|-------|-------|-------|----------------|--|------------------------|
| Erlotinib          |           | X-----X |      |      |      |      |       |       |       |       |       |                |  |                        |
| Oral Vinorelbine   |           | X-----X |      |      |      |      |       |       |       |       |       |                |  |                        |
| Informed consent   | X         |         |      |      |      |      |       |       |       |       |       |                |  |                        |
| Demographics       | X         |         |      |      |      |      |       |       |       |       |       |                |  |                        |
| Medical history    | X         |         |      |      |      |      |       |       |       |       |       |                |  |                        |
| Concurrent meds    | X         | X-----X |      |      |      |      |       |       |       |       |       |                |  |                        |
| Physical exam      | X         | X       | X    | X    | X    | X    | X     | X     | X     | X     | X     | X e |  | X                      |
| Vital signs        | X         | X       | X    | X    | X    | X    | X     | X     | X     | X     | X     | X e |  | X                      |
| Height             | X         |         |      |      |      |      |       |       |       |       |       |                |  |                        |
| Weight             | X         | X       |      | X    |      | X    |       | X     |       | X     |       | X e |  | X                      |
| Performance status | X         | X       |      | X    |      | X    |       | X     |       | X     |       | X e |  | X                      |

|                                                                                                                                                                                                                                                                                                                                                                                                                                                                       |                 |                                                                                                                                                                                                                                       |   |   |   |   |   |   |   |   |   |                |  |                |
|-----------------------------------------------------------------------------------------------------------------------------------------------------------------------------------------------------------------------------------------------------------------------------------------------------------------------------------------------------------------------------------------------------------------------------------------------------------------------|-----------------|---------------------------------------------------------------------------------------------------------------------------------------------------------------------------------------------------------------------------------------|---|---|---|---|---|---|---|---|---|----------------|--|----------------|
| CBC w/diff, plts                                                                                                                                                                                                                                                                                                                                                                                                                                                      | X               | X                                                                                                                                                                                                                                     | X | X | X | X | X | X | X | X | X | X e |  | X              |
| Serum chemistry b                                                                                                                                                                                                                                                                                                                                                                                                                                          | X               | X                                                                                                                                                                                                                                     | X | X | X | X | X | X | X | X | X | X e |  | X              |
| EKG (as indicated)                                                                                                                                                                                                                                                                                                                                                                                                                                                    | X               |                                                                                                                                                                                                                                       |   |   |   |   |   |   |   |   |   |                |  |                |
| Adverse event evaluation                                                                                                                                                                                                                                                                                                                                                                                                                                              |                 | X -----X                                                                                                                                                                                                                              |   |   |   |   |   |   |   |   |   |                |  | X              |
| Tumor measurements                                                                                                                                                                                                                                                                                                                                                                                                                                                    | X               | Tumor measurements are repeated every 6 weeks for the first 6 months, then every 12 weeks thereafter unless disease progression. Documentation (radiologic) must be provided for patients removed from study for progressive disease. |   |   |   |   |   |   |   |   |   |                |  | X d |
| Radiologic evaluation                                                                                                                                                                                                                                                                                                                                                                                                                                                 | X               | Radiologic measurements should be performed every 6 weeks for the first 6 months, then every 12 weeks thereafter unless disease progression.                                                                                          |   |   |   |   |   |   |   |   |   |                |  | X d |
| B-HCG                                                                                                                                                                                                                                                                                                                                                                                                                                                                 | X c  |                                                                                                                                                                                                                                       |   |   |   |   |   |   |   |   |   |                |  |                |
| Other tests, as appropriate                                                                                                                                                                                                                                                                                                                                                                                                                                           |                 |                                                                                                                                                                                                                                       |   |   |   |   |   |   |   |   |   |                |  |                |
| Pharmacokinetic studies                                                                                                                                                                                                                                                                                                                                                                                                                                               | See section 9.0 |                                                                                                                                                                                                                                       |   |   |   |   |   |   |   |   |   |                |  |                |
| a: vinorelbine and erlotinib: Dose as assigned; oral.
b: Albumin, alkaline phosphatase, total bilirubin, bicarbonate, BUN, chloride, creatinine, glucose, LDH, potassium, total protein, SGOT[AST], SGPT[ALT], sodium.
c: Serum pregnancy test (women of childbearing potential).
d: Off-study evaluation.
e: For subjects who respond or stable at disease , cycle duration will extend from 3 weekly to 6 weekly after 6 months (8cycles) of treatment. |                 |                                                                                                                                                                                                                                       |   |   |   |   |   |   |   |   |   |                |  |                |

